| 0.02                       | 0.0125                | 0.01625            | 0.0075                 | 4461                         | 201                            | 12462                        |
| 0.0225                     | 0.015                 | 0.01875            | 0.0075                 | 5134                         | 246                            | 15252                        |
| Power = 0.9         |                       |                    |                        |                              |                                |                              |
| 0.015                      | 0.005                 | 0.01               | 0.01                   | 2079                         | 77                             | 4774                         |
| 0.02                       | 0.01                  | 0.015              | 0.01                   | 3103                         | 124                            | 7688                         |
| 0.025                      | 0.015                 | 0.02               | 0.01                   | 4117                         | 180                            | 11160                        |
| 0.03                       | 0.02                  | 0.025              | 0.01                   | 5121                         | 245                            | 15190                        |
| 0.015                      | 0.0075                | 0.01125            | 0.0075                 | 4154                         | 182                            | 11284                        |
| 0.0175                     | 0.01                  | 0.01375            | 0.0075                 | 5065                         | 241                            | 14942                        |

† A one sided  $\alpha = 0.025$  is required for a 95% CI. The number of clusters is assumed to 31, the ICC = 0.01 and the IPC=0.008.

‡ Table does not account for an estimation of loss to follow-up

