### **Outcome variables**

The primary outcome of the study is symptomatic VTE within 90 days of surgery. Secondary outcomes are:

- Deep vein thrombosis (DVT) only (total, below-knee and above-knee) within 90 days
- Pulmonary embolism (PE) only within 90 days
- Readmission related to the original surgery or associated treatment (including bleeding and VTE-related) within 90 days
- Reoperation on the same joint within 90 days and within 6 months of surgery
- Major bleeding events within 90 days defined as bleeding events resulting in readmission, reoperation or death
- Death within 90 days
- Change in patient-reported pain, function and health status measures as measured by the Oxford Hip Score (OHS), Oxford Knee Score (OKS), EQ-5D score and the EQ-VAS from baseline to 6 months postoperatively

Outcome and demographic data were collected preoperatively (demographics, patient reported pain, function and health status) and at 90 days and 6 months postoperatively. Data for all primary and secondary outcomes are patient-reported (except for death). All patients who responded 'yes' to having experienced a VTE or a secondary operation within 6 months had this result verified by AOANJRR staff through contact with treating doctors and hospitals. A random audit of 200 patients who did not report a VTE event was undertaken to detect the false negative reporting rate. All data collected for registered patients specific to CRISTAL have been outlined in the published protocol [15]. Mortality data were collected through linkage between the AOANJRR and the National Death Index.

In the published protocol [15], mortality was to be measured at 90 days and 6 months. Due to the lack of sensitivity in measuring VTE-related mortality at 6 months, and due to the lag in data availability for mortality, we will only analyse mortality at 90 days [17].

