**Legend:**

Abbreviations: *HA* hip arthroplasty, *KA* knee arthroplasty, *THA* total hip arthroplasty, *TKA* total knee arthroplasty, *OA* osteoarthritis

† Study drug excluded for patients who already on long-term anticoagulation (specifically a novel oral anticoagulant – NOAC, warfarin or dual antiplatelet therapy – DAPT) and those who have a medical contraindication

Each outcome (primary and secondary) will be assessed for populations 1, 2, 3 and 4 listed in Figure 1. Mortality will be assessed for all populations (including population 5). The primary objective of the study as outlined in the published protocol [15], was the analysis of population 1 only (registered patients undergoing primary THA or TKA for a diagnosis of OA who are eligible to receive the study drug), as this was the focus of the sample size calculation. This population will remain the focus of the main analyses.

Population 1 was chosen as the focus of the main analysis as these patients represent the majority of patients undergoing HA or KA procedures and there are known differences in outcomes and co-morbidities with other diagnoses (e.g., fracture, tumour), which could confound the primary outcome [22].

For the primary end point of VTE, the following subgroup analyses will be conducted within the corresponding populations listed:

- Type of joint replacement: primary THA compared to primary TKA – population 1
- Bilateral arthroplasty: patients undergoing simultaneous bilateral arthroplasty compared to those who are not – population 1
- Revision arthroplasty: patients undergoing revision hip or knee arthroplasty compared to those undergoing primary arthroplasty – population 3
- Prior history of VTE: patients with a prior history of VTE compared to those without – population 1

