## MAIN ANALYSES

The main analyses will include the primary and secondary outcomes for registered patients eligible to receive the study drug undergoing THA or TKA for a diagnosis of OA (population 1). In addition, the primary and secondary outcomes will be analysed for populations 2, 3 and 4. Mortality will also be analysed for population 5 (see “Additional analyses” below).

For the primary outcome, the analysis will test the between-group difference of cases developing a symptomatic VTE within 90 days for non-inferiority of aspirin at a margin of 1%. Cluster summary methods will be used to estimate the treatment effect using cluster level differences. These have been shown to be appropriate for cluster-randomised crossover trials with rare outcomes, and the intracluster and interperiod correlation coefficients expected in this trial. The crossover difference per cluster is the mean outcome for the intervention period minus the mean outcome for the control period. In a linear regression of cluster differences on treatment sequence, the treatment effect estimate is the intercept. To account for potential unequal cluster sizes, a cluster size weighted estimator will be used with harmonic mean weights of the number of patients in the two periods, which was the same method used in the interim analyses for incomplete crossover [25, 26]. Treatment effects will be presented as absolute risk differences and 95% confidence intervals will be examined to determine whether the non-inferiority margin has been met and whether superiority of one drug can be concluded. The primary outcome will be presented in Table 3 and Figure 4 will be used to demonstrate whether the non-inferiority margin has been met for the population 1 [30].

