The secondary outcomes will investigate non-VTE complications (death, re-operation, readmission and major bleeding events) within 90 days, and reoperation and patient-related pain and function at 6 months (OHS, OKS, EQ-5D and EQ-VAS). Cluster summary methods will be used within an intention-to treat approach. For binary outcomes, the cluster mean per period will be the proportion of patients who had the outcome, while for continuous outcomes such as pain score, the cluster mean will be the mean outcome. Treatment effects will be presented as absolute risk differences and 95% confidence intervals to determine if one treatment is superior to the alternative. Results for the secondary outcomes in population 1 will be presented in tabular form (Table 3) and results for the primary and secondary outcomes in populations 2, 3 and 4 in Table 4.

Due to the early stopping of the trial, final analyses of the primary and secondary outcomes will use the same composite method as the interim analyses which accounts for clusters with incomplete as well as no crossover, with 95% confidence intervals. No bias is expected from early stopping if the patients included in the trial are not systematically different from later patients who would have been included after the trial was stopped. Our composite analysis method accounts for clusters which either had incomplete crossover and or did not crossover. However, the lower sample size and unequal cluster sizes decreases the precision of the outcome estimates. Since we used cluster weighted estimates to account for unequal cluster sizes and increased the initial sample size by 27% above the minimum required, the loss of precision will be mitigated. The trial was stopped based on the Haybittle-Peto

boundary of 0.001, so we anticipate the final analysis using 95% confidence intervals will have sufficient power.

**Table 3.** Outcomes for population 1

| Outcome                                            | LMWH Allocation
(n = X) | Aspirin Allocation
(n = X) | Absolute Risk Difference | 95% Confidence Interval | p-value |
|----------------------------------------------------|----------------------------|-------------------------------|--------------------------|-------------------------|---------|
| Any Venous thromboembolism                  | n (%)                      | n (%)                         | X                        | X – X                   |         |

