| Type of Venous thromboembolism              |                            |                               |                          |                         |         |
| Pulmonary embolism                                 | n (%)                      | n (%)                         | X                        | X – X                   |         |
| Deep venous thrombosis                             | n (%)                      | n (%)                         | X                        | X – X                   |         |
| Both Pulmonary embolism and deep venous thrombosis | n (%)                      | n (%)                         | X                        | X – X                   |         |
| Above knee deep venous thrombosis                  | n (%)                      | n (%)                         | X                        | X – X                   |         |
| Below knee deep venous thrombosis                  | n (%)                      | n (%)                         | X                        | X – X                   |         |
| Death                                              | n (%)                      | n (%)                         | X                        | X – X                   |         |
| Re-operation (90d)                                 | n (%)                      | n (%)                         | X                        | X – X                   |         |
| Reoperation (6 months)                             | n (%)                      | n (%)                         | X                        | X – X                   |         |
| Re-admission                                       | n (%)                      | n (%)                         | X                        | X – X                   |         |
| Major Bleeding                                     | n (%)                      | n (%)                         | X                        | X – X                   |         |
| Pain and Function (median and IQR) †    |                            |                               | X                        | X – X                   |         |
| Oxford Hip Score                                   | X (X – X)                  | X (X – X)                     | X                        | X – X                   |         |

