## **ADDITIONAL ANALYSES**

### **Mortality Analysis**

In addition to analysing between-group mortality for populations 1, 2, 3 and 4, the between-group 90-day mortality will be analysed for two further populations:

3. All patients undergoing HA or KA over the duration of the study at participating hospitals, regardless of whether they were registered (total population described above, population 5)
4. All patients undergoing elective THA or TKA over the duration of the study at participating hospitals regardless of whether they were registered (a subset of population 5)

Analysing these additional populations will assess the effect of implementing the VTE prophylaxis protocol on mortality at an institutional/departmental level (the unit of randomisation), on an intention-to-treat basis.

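### Each secondary outcome is judged for superiority on its own unadjusted 95% interval, in up to four nested populations, with nothing limiting the overall chance of a false claim

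*Supplement*

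**What the plan says.** The final SAP names one primary contrast: symptomatic VTE within 90 days in population 1, tested against a 1% margin. Its next paragraph, under Main Analyses, takes up the secondary outcomes, described as "non-VTE complications (death, re-operation, readmission and major bleeding events) within 90 days, and reoperation and patient-related pain and function at 6 months", with the four scores OHS, OKS, EQ-5D and EQ-VAS. It then gives the rule for reading them: "Treatment effects will be presented as absolute risk differences and 95% confidence intervals to determine if one treatment is superior to the alternative". Tables 3 and 4 provide a p-value column for these rows.

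The repetition across populations is stated twice. Under Patient Populations and Subgroups for Analyses: "Each outcome (primary and secondary) will be assessed for populations 1, 2, 3 and 4 listed in Figure 1". Under Main Analyses: "In addition, the primary and secondary outcomes will be analysed for populations 2, 3 and 4". For death, the Mortality Analysis section adds that "the between-group 90-day mortality will be analysed for two further populations".

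The number of secondary outcomes depends on where one looks:
- The Main Analyses paragraph names nine, all non-VTE.
- The Outcome Variables section lists 13. It adds PE and three DVT outcomes: "Deep vein thrombosis (DVT) only (total, below-knee and above-knee) within 90 days".
- Table 3 has 14 secondary rows, the extra one being "Both Pulmonary embolism and deep venous thrombosis".

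No passage of the final SAP or final protocol adjusts for multiplicity, makes one secondary test depend on another, or calls these outcomes exploratory.

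**The concern.** The clause about determining superiority is a decision rule, applied to one outcome at a time. Followed as written, any secondary interval that excludes zero licenses a statement that one drug is superior on bleeding, death, readmission, reoperation or function. With many outcomes and several overlapping populations, a chance exclusion somewhere is likely even if the drugs do not differ on any of them.

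This matters here because comparing safety is a stated secondary aim (final protocol, section 2.5), and the results are meant to inform guidelines and influence practice (section 4.10). A chance difference in one harm, in one of four nested populations, could be reported as an established advantage.

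**Working it through.** **What level each interval carries.** The documents give no family-wise figure for the secondary outcomes, so there is none to reproduce. The per-comparison level can be confirmed. The footnote to Table 1 of the final protocol says that a one-sided 0.025 "is required for a 95% CI", which is two-sided 5%. The plan's 4,117 per group follows at that level with 90% power and rates of 2.5% and 1.5%:

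[1.960·√(2·0.02·0.98) + 1.2816·√(0.025·0.975 + 0.015·0.985)]² / 0.01² = (0.3881 + 0.2536)² / 0.0001 ≈ 4,117.

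**Count.** Main Analyses paragraph: death, reoperation, readmission and major bleeding at 90 days (4), reoperation at 6 months (1), four scores (4), so k = 9. Table 3: these 9 plus five VTE-type rows, so k = 14.

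**Population 1, no true difference in any outcome counted.** With independent outcomes the chance of at least one interval excluding zero is 1 − 0.95^k:
- k = 9: 1 − 0.95⁹ = 0.370
- k = 14: 1 − 0.95¹⁴ = 0.512

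With a common correlation ρ between the test statistics it is

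1 − ∫ φ(u)·[Φ((1.96 − √ρ·u)/√(1−ρ)) − Φ((−1.96 − √ρ·u)/√(1−ρ))]^k du.

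The documents give no correlation, so ρ is an assumption, shown as a range.

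**Populations 1 to 4.** These are nested. The final protocol (section 3.3) aims for 250 patients eligible for the primary analysis per group at each site and expects 300 for all arthroplasties, so I took population 1 as 250 and population 4 as 300. The sizes of populations 2 and 3 are not given; I tried three spacings between those limits. The correlation between populations for one outcome is √(n smaller / n larger). For populations 1 and 4 this is √(250/300) = 0.913, the lowest of the six pairs. The full correlation matrix is the product of the two structures, simulated with 400,000 draws per case.

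| Outcomes counted | ρ | Population 1 | Populations 1–4 |
|---|---|---|---|
| 9 (non-VTE) | 0 | 37% | 51–52% |
| 9 | 0.5 | 27% | 38–39% |
| 9 | 0.7 | 20% | 29% |
| 14 (Table 3) | 0 | 51% | 67–68% |
| 14 | 0.5 | 35% | 48–49% |
| 14 | 0.7 | 25% | 35% |

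The ranges in the last column span the three spacings. The two additional mortality populations are not included and would add a little.

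**Is the error limited elsewhere?**
- The Order of Planned Analyses section is a running order. It lists the primary and secondary outcomes of population 1 together and ties no test to an earlier result.
- Population 1 is called the focus of the main analyses, but no error rule is attached to that.
- The Haybittle-Peto boundary of 0.001 applies to interim looks at the primary outcome only.

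**The case against.** The plan does rank its evidence: one primary outcome, one time point, one lead population. Section 3.15 of the final protocol places the wider populations among secondary analyses and gives them a different purpose, the effect of applying the protocol at departmental level. Many trials report secondary outcomes with unadjusted intervals, and most of the outcomes here are harms, where strict gatekeeping could hide a real signal. This argues against imposing a testing hierarchy. It does not answer the point, because the SAP goes beyond reporting intervals and says that they determine superiority.

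Several stronger readings are tempting but not supported:
- **That a stated 5% rate is inflated by some multiple.** The documents state no rate for the set; 5% is only the per-comparison level that a 95% interval implies.
- **That all 14 rows of Table 3 clearly fall under the superiority rule and are all null.** The paragraph containing the rule names nine non-VTE outcomes. The five VTE-type rows are parts of the primary outcome, and the trial stopped because the boundary for VTE was met, so a difference there need not be false.
- **That 14 × 4 = 56 comparisons behave independently.** That would give 1 − 0.95⁵⁶ = 94%, but the populations are nested and share most of their patients. Applying the single correlation for populations 1 and 4 to every pair would also overstate the result.
- **That Table 4 displays every outcome in every population.** As readable, its shell has no EQ-VAS row in populations 2 to 4 and no EQ-5D row in the final version, although the text calls for all outcomes.

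**Conclusion.** The point holds, as a wording fault with real consequences. The final SAP attaches a superiority decision to each secondary outcome at an unadjusted 95% level and repeats the outcomes in four nested populations, with no control and no exploratory label.

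On the nine outcomes that the paragraph names, the chance of at least one false superiority claim is about 27% in population 1 (20% to 37%) and about 39% over populations 1 to 4 (about 30% to 52%). Counting all 14 rows gives about 35% (25% to 51%) and about 48% (35% to 68%), with the reservation that the VTE-type rows may not be null. These figures assume no true difference in any outcome counted, outcome correlations from 0 to 0.7 centred on 0.5, and population sizes between 250 and 300. A true difference on some outcome would remove that row from the count and lower the figure.

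A reader might infer that the primary conclusion is weakened. It is not: the non-inferiority test of VTE in population 1 is a single named comparison and is unaffected.

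**What to change.** In the secondary-outcomes paragraph of Main Analyses, replace the clause about determining superiority with estimation wording, for example that risk differences (mean differences for the scores) and 95% confidence intervals will be reported to describe the size and precision of the treatment effect. Add one statement: secondary outcomes, and all outcomes in populations 2 to 5, are reported with 95% intervals not adjusted for multiplicity, are exploratory, and will not support superiority claims.

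The change affects SAP text only. No analysis, estimate or interval changes and no further data are needed. The downside is that the trial gives up formal superiority claims on secondary outcomes. Removing the p-value columns for these rows, or naming a short fixed testing sequence, is optional and not needed to resolve the point.

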### **Power and sample size**

For the sample size calculation in CRISTAL, we used an estimated overall event rate of 2% (based on the current available literature) [18, 19], a non-inferiority margin of 1% (based on clinician opinion and a recent randomised controlled trial) [12], i.e., an event rate of 2.5% for aspirin and 1.5% for LMWH, a power of 90% and a one-sided significance level of 0.025. For an individual randomised trial, this yields a sample size of 4,117 per treatment group or a total of 8,234 patients. For a cluster-randomised crossover trial with an intracluster correlation of 0.01, an interperiod correlation of 0.008 and 31 clusters, the required sample

size is 11,160 patients, or 180 patients per arm for each cluster [20, 21]. However, due to the uncertainty surrounding the event rate and intracluster and interperiod correlations, loss to follow-up, uneven recruitment rates leading to unequal cluster sizes or clusters dropping out of the study, we aimed to register 251 patients eligible for the primary objective of the study, providing a total of 15,562 patients. This figure allowed for a maximum 27% reduction in the above sample size calculation [15], however, actual loss to follow-up was expected to be less than this.

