### **Interim analysis**

An interim analysis was not initially planned, as both treatments are considered standard practice for VTE prophylaxis in Australia and the trial is investigating an adverse event as the primary outcome. However, due to concerns of an increased adverse event rate (symptomatic VTE and death) in one of the prophylaxis groups, a Data Safety Monitoring

Board (DSMB) was convened one year into patient recruitment. The DSMB consisted of an orthopaedic surgeon, a haematologist and a statistician, all independent of the trial.

The DSMB were advised by the Trial Management Committee (TMC) to conduct an interim analysis. In conjunction with the DSMB (prior to the interim analysis), the TMC applied the Haybittle-Peto stopping rule of a two-sided significance of 0.001 for the primary outcome in the population 1 [23, 24]. This stopping rule was chosen as it does not require adjustment of the significance threshold for the final analysis and allows further interim analyses using the same threshold (if required).

After the first interim analysis (in September 2020), the DSMB recommended continuing the trial and performing a second interim analysis in November 2020. After reviewing the second interim analysis, the DSMB recommended ceasing patient recruitment as the stopping rule had been met. The study ceased recruiting patients in December 2020 and sites reverted to their usual VTE prophylaxis pathways.

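### Similar early and later patients do not remove the selection caused by stopping at p<0.001, and the 27% cushion the SAP cites was a planned 39% whose target was not reached

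*Supplement*

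**What the plan says.** The final SAP, Interim analysis, describes two unplanned looks, in September and November 2020, using a Haybittle-Peto boundary of two-sided 0.001 on the primary outcome in population 1. After the second, "the DSMB recommended ceasing patient recruitment as the stopping rule had been met". Registration ended in December 2020 with crossover incomplete.

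The early-stopping paragraph under Main analyses keeps the composite estimator from the interim looks, with ordinary 95% confidence intervals, and gives three assurances:

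- On bias: "No bias is expected from early stopping if the patients included in the trial are not systematically different from later patients" who would have joined had the trial continued.
- On precision: it concedes that the smaller sample and unequal clusters cost precision, but says this is mitigated, partly because the investigators "increased the initial sample size by 27% above the minimum required".
- On power: the trial stopped at 0.001, "so we anticipate the final analysis using 95% confidence intervals will have sufficient power".

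Power and sample size in the same SAP gives a minimum of 11,160 (180 per arm per cluster) and a target of 15,562 (251 per arm per cluster). There, 27% is the largest reduction the target was meant to absorb. No stopping-adjusted estimate or interval is planned, and there is no caveat about overestimation.

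**The concern.** The condition in the first assurance is about who was recruited. Bias from a data-driven stop has another source: the trial ends only when the observed difference is extreme, so a moderate true effect is reported from those runs in which chance pushed it up. This happens even when every patient is drawn from the same population. The reason the SAP gives for choosing Haybittle-Peto is that the final significance threshold needs no adjustment; that concerns type I error, not estimation.

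The second assurance turns a tolerated loss into an increase, and credits a planned target with protecting a trial that stopped short of it. The third infers power from an observed result on one outcome, in a paragraph that also covers the secondary outcomes.

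At stake is how the risk difference is read against the 1-point margin, and how far null findings on bleeding, death and reoperation can be trusted.

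**Working it through.** **1. The plan's own sample sizes reproduce.** Inputs (final SAP, Power and sample size): "an event rate of 2.5% for aspirin and 1.5% for LMWH, a power of 90% and a one-sided significance level of 0.025". A two-proportion formula gives 4,117 per arm, agreeing with "this yields a sample size of 4,117 per treatment group or a total of 8,234 patients". With an intracluster "correlation of 0.01, an interperiod correlation of 0.008 and 31 clusters":

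m = n(1 − ICC) / [k − n(ICC − IPC)] = 4,117 × 0.99 / (31 − 4,117 × 0.002) = 179.03, rounded up to 180.

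180 × 31 × 2 = 11,160 and 251 × 31 × 2 = 15,562. Both match.

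**2. The 27% does not.**

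- Increase over the minimum: 15,562 / 11,160 = 251 / 180 = 1.394, or 39%.
- A 27% increase would be 11,160 × 1.27 = 14,173.
- Tolerable loss from the target: 1 − 11,160 / 15,562 = 28.3%. A 27% loss leaves 15,562 × 0.73 = 11,360, still above 11,160.

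So 27% is sound as a tolerated reduction and wrong as an increase.

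**3. Selection at the boundary.** Two-sided 0.001 means |Z| > 3.29. Full-information standard error, from the design: 1.0 / (1.960 + 1.282) = 0.308, taken as 0.31 points. The smallest difference that crosses at look 2 is 3.29 × 0.31 / √t2, where t2 is the information fraction at that look.

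The documents give no information fractions, so three schedules are assumed (look 1 / look 2 / final, the last including data arriving after the stop). Simulated normal paths with independent increments and one constant true effect satisfy the SAP's condition exactly. Results are for trials that first cross at look 2, in points:

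| Schedule | Smallest crossing difference | Truth 0.75: mean (95% CI coverage) | Truth 1.0: mean (coverage) | Truth 1.5: mean |
|---|---|---|---|---|
| 30/40/55% | 1.61 | 1.48 (66%) | 1.56 (87%) | 1.72 |
| 45/55/65% | 1.38 | 1.37 (79%) | 1.42 (97%) | 1.52 |
| 60/70/85% | 1.22 | 1.21 (90%) | 1.26 (99%) | 1.37 |

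A look-2 stop occurs in about 2 to 4% of trials if the truth is 0.75 and 6 to 9% if it is 1.0. Averaged over every outcome of the design, including trials that run to completion, the bias at these two true values is about 2 to 5% and coverage about 94 to 95%.

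If full information is instead set at the 251 target, the effective number per arm is 31 × 251 / (0.99 + 251 × 0.002) = 5,215, and the standard error is 0.308 × √(4,117 / 5,215) = 0.27. The conditional means for the earliest and latest schedules are then lower: 1.41 and 1.14 for a true 1.0, and 1.33 and 1.09 for a true 0.75.

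**4. Power.** In the same model, the final 95% interval excludes zero in more than 99% of look-2 stops for true effects of 0.5 to 1.5 points. This follows from having crossed 0.001 on that outcome. No boundary was set on readmission, reoperation, bleeding or the patient-reported scores, and crossing the primary boundary carries no information about their precision.

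**The case against.** Several stronger readings are tempting, and the documents do not support them.

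- *The SAP claims flatly that there is no bias.* Its sentence is conditional, and it discloses the unplanned looks, the boundary and the early stop. The fault is that the condition, even if met, does not deliver the conclusion.
- *The result is overstated by a known amount.* Neither the true effect nor the information at each look is given. The figures condition on a look-2 stop, which is uncommon for moderate effects. At a true 1.0, coverage in the two later schedules is above nominal. Near 1.5 points the bias is small. It reverses for larger effects, because an effect that large which had not crossed at look 1 was running low: in the middle schedule a true 1.75 averages 1.58.
- *The extra patients were never recruited.* Enrolment is not stated and could lie above or below 11,160. Sites that crossed over on meeting the first-arm target had reached 251, not 180, in that period. What can be said is that the inflated target was not reached.
- *The 27% slip undermines the sample size.* It changes no calculation; 11,160 and 15,562 both stand.
- *The power sentence is empty.* For the primary outcome it is loose but largely harmless; it fails for the secondary outcomes.

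It is also fair to say that adjustment is not mechanical. Between looks the composite estimator moves clusters from the parallel to the crossover component, so independent increments are not assured, and the looks were prompted by concern about events in one group. An adjusted figure has assumptions of its own, so it belongs in a sensitivity analysis.

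**Conclusion.** The point stands in limited form and should be fixed. Confidence is high on the principle and the arithmetic, not on the size of the bias. Exchangeability of early and later patients does not remove selection from a stop that required |Z| > 3.29. With a full-information standard error of 0.31 points and the assumed schedules, the mean final estimate given a look-2 stop exceeds a true 1.0 by 26 to 56%. For a true 0.75, interval coverage falls to 66 to 90%. The increase over the minimum was 39%, not 27%, and cannot be cited in full as protecting precision once recruitment stopped short of it. The power assurance is not supported for the secondary outcomes. None of this shows that the trial's actual estimate is wrong; it shows that the SAP's reasons for not qualifying it are insufficient.

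**What to change.** - Replace the no-bias sentence with a caveat that an estimate obtained after stopping at the boundary may overstate a moderate effect, even if the patient mix did not change.
- Change the 27% to 39% planned, target not reached, or reword it as the tolerated loss.
- Delete the power sentence or confine it to the primary outcome.
- Report the achieved number in population 1 and the information available at each look and at the final analysis.
- Keep the planned estimate and 95% interval as primary. Add a stopping-adjusted estimate and interval (conditional, or stage-wise median-unbiased) as a sensitivity analysis, stating its assumptions: information at each look, overrun after the stop, and approximately independent increments for the composite estimator.

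The cost is wording changes and a modest extra analysis, with some work to justify the increments assumption. The downside is a possibly less extreme estimate shown beside the headline one.
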